**10.4 Data Handling and Confidentiality**

- Data will be stored in a secured electronic data capture (EDC) system.
- Personal identifiers will be replaced with unique study IDs.
- Data retention period: Minimum of 10 years post-study completion.

**10.5 Statistical Analysis Plan**

1. **Baseline Characteristics:** Descriptive statistics for demographic and clinical characteristics.
2. **Primary Endpoint Analysis:**
   - Incidence of AF and ventricular tachycardia will be analyzed using proportion estimates.
   - Confidence intervals (95% CI) will be reported.
3. **Secondary Endpoint Analysis:**
   - Kaplan-Meier survival curves for time-to-event analyses.
   - Cox regression models for risk factor assessment.
4. **Safety Analysis:**
   - AE incidence and severity will be analyzed descriptively.

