**Endpoints**

- **Primary Endpoint**
  Proportion of patients in whom AF or non-sustained or sustained ventricular tachycardia is detected

Defined as the proportion of patients (in the analysis population) who exhibit the following on ILR:

- - AF of ≥6 minutes duration
  - Non-sustained VT: rate >150 bpm, ≥16 consecutive beats, ≤30 seconds
  - Sustained VT: rate >150 bpm, ≥30 seconds
- **Secondary Endpoints**
  - Proportion of patients with pauses ≥4.5 seconds
  - Proportion of patients with bradycardia <30 bpm
  - Proportion of patients with high-grade AV block
  - Proportion of patients who received a permanent pacemaker, ICD, catheter ablation, or antiarrhythmic drug therapy
  - All-cause mortality rate
  - Cardiovascular mortality rate
  - Proportion of patients requiring hospitalization due to cardiovascular disease or heart failure
  - Proportion of patients who experienced stroke
- **Safety Endpoints**
  - Incidence of adverse events related to ILR implantation
  - Incidence of device malfunctions

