##### 7.1.5 End of the Study

- At 3 years post-implantation, the subject completes the protocol observation period, and the ILR is explanted.
- If an adverse event or device malfunction (e.g., battery depletion) necessitates explantation, the study observation ends at that time.
- If a new device (e.g., a permanent pacemaker) is implanted, rendering ILR monitoring moot, ILR is explanted, and observation ends.
- If follow-up is no longer feasible, the ILR is explanted, and observation ends.
- Explantation is generally performed on an outpatient basis with local anesthesia. The removed ILR is discarded per institutional procedures.
- The MyCareLink Relay Home Communicator is discarded as non-burnable trash.

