##### 8.1.2 Secondary Endpoints

1. Proportion of patients with pauses ≥4.5 s
2. Proportion of patients with bradycardia <30 bpm
3. Proportion of patients with high-grade AV block
4. Proportion of patients receiving pacemaker, ICD, ablation, or antiarrhythmic therapy
5. All-cause mortality
6. Cardiovascular mortality
7. Proportion with hospitalizations for CV disease/HF
8. Proportion who experienced stroke

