**9.3 Statistical Analysis of Safety Endpoints**

- The frequency and incidence rate of AEs and device malfunctions will be calculated.
- Kaplan-Meier survival analysis may be conducted for time-to-event data.
- Subgroup analysis will be performed based on subject demographics, comorbidities, and treatment history.

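### Section 10.5 names Kaplan-Meier as the only time-to-event estimator for secondary endpoints without saying that death competes with all of them except all-cause mortality

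*Protocol*

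**What the plan says.** Section 10.5, item 3, lists two methods for the secondary endpoints: "Kaplan-Meier survival curves for time-to-event analyses" and "Cox regression models for risk factor assessment". Estimates of proportions are assigned only to the primary endpoint, in item 2. Section 9.3 adds an optional use for safety: "Kaplan-Meier survival analysis may be conducted for time-to-event data". Competing risks and cumulative incidence are not mentioned anywhere. Section 10.5 does not say which secondary endpoints are time-to-event or whether deaths are censored.

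Six of the eight secondary endpoints are defined as shares of patients, for example "Proportion of patients who received a permanent pacemaker, ICD, catheter ablation, or antiarrhythmic drug therapy" (Section 1, Endpoints) and "Proportion who experienced stroke" (Section 8.1.2). The other two are mortality endpoints: "All-cause mortality rate" (Section 1, Endpoints) and "Cardiovascular mortality" (Section 8.1.2).

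Section 7.1.5 ends follow-up early in some patients who are still alive: "If a new device (e.g., a permanent pacemaker) is implanted, rendering ILR monitoring moot, ILR is explanted, and observation ends". Section 7.2.2 collects the date of death and whether it was cardiovascular, and the dates of hospitalisation, stroke and device, ablation or drug therapy.

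**The concern.** Only all-cause mortality has no competing event. Non-cardiovascular death precludes cardiovascular death. Any death precludes a later first stroke, hospitalisation, therapy or recorded bradyarrhythmia. A Kaplan-Meier curve that censors these deaths estimates the risk in a setting where the deaths do not happen. It does not estimate the share of enrolled patients who have the event, although that share is how most of these endpoints are defined.

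Two things are at stake. First, the report could carry two different figures for one endpoint, a crude proportion and a higher Kaplan-Meier risk, and the cause-specific mortality risks could add up to more than all-cause mortality. Second, Section 3 says that promising results may lead to a further trial, and risks that are too high are poor planning inputs. Deaths are to be expected: the patients have heart failure with reduced ejection fraction, follow-up lasts up to 3 years, and death is itself a secondary endpoint.

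**Working it through.** **Inputs from the protocol.** There are 35 patients in one arm (Section 10.2), a main analysis at 1 year and a final analysis at 3 years (Section 8.2). No event rate, death rate or precision target is given, so the protocol has no figure of its own to reproduce here.

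**Assumptions.** Hazards are constant and there is no censoring other than death and the end of follow-up. The 3-year event risks by Kaplan-Meier are set at 5% (stroke), 15% (cardiovascular death), 20% (device, ablation or drug therapy) and 40% (cardiovascular or heart failure hospitalisation). Competing death at 3 years ranges from 5% to 30%. For cardiovascular death only non-cardiovascular death competes, so the upper end of that range is more extreme there.

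**Formulas.** With r the 3-year event risk and d the 3-year competing-death risk, the yearly hazards are λ1 = −ln(1 − r)/3 and λ2 = −ln(1 − d)/3. At time T:

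- 1 − Kaplan-Meier = 1 − exp(−λ1·T)
- cumulative incidence = λ1/(λ1 + λ2) × [1 − exp(−(λ1 + λ2)·T)]

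**Worked case.** Take r = 40%, d = 20% and T = 3. Then 3λ1 = 0.5108, 3λ2 = 0.2231 and their sum is 0.7340. The cumulative incidence is 0.5108/0.7340 × (1 − 0.60 × 0.80) = 0.696 × 0.52 = 36.2%, against 40.0% by Kaplan-Meier.

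**Results at 3 years.**

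| Endpoint | 1 − KM | Cumulative incidence with competing death 5% / 10% / 20% / 30% | Excess, points | Patients of 35 |
|---|---|---|---|---|
| Stroke | 5.0% | 4.9 / 4.7 / 4.5 / 4.2% | 0.1 to 0.8 | 0.04 to 0.28 |
| Cardiovascular death | 15.0% | 14.6 / 14.3 / 13.5 / 12.7% | 0.4 to 2.3 | 0.13 to 0.81 |
| Device, ablation or drug therapy | 20.0% | 19.5 / 19.0 / 18.0 / 16.9% | 0.5 to 3.1 | 0.17 to 1.07 |
| Hospitalisation | 40.0% | 39.1 / 38.1 / 36.2 / 34.2% | 0.9 to 5.8 | 0.32 to 2.05 |

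**Results at 1 year.** The largest case (hospitalisation, 30% competing death by 3 years) gives 15.7% against 14.8%, an excess of 0.9 points. All other cases are smaller.

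**Simulation check.** Five combinations were run, with 4,000 trials of 35 patients each and follow-up complete to 3 years apart from death. In that setting the crude proportion equals the Aalen-Johansen estimate. Mean 1 − Kaplan-Meier against mean crude proportion was 20.0% against 18.0% (event 20%, competing death 20%), 40.1% against 36.2% (40%, 20%) and 39.9% against 34.1% (40%, 30%). Kaplan-Meier fell below the crude proportion in no simulated trial.

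**Sampling error for comparison.** The standard deviation of 1 − Kaplan-Meier across the simulated trials was about 4 to 9 points. The exact 95% confidence interval is 8.4% to 36.9% for 7 of 35 patients and 23.9% to 57.9% for 14 of 35.

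**Coherence of the mortality endpoints.** Kaplan-Meier risks of 15% for cardiovascular and 20% for non-cardiovascular death add to 35%, while all-cause mortality is 1 − 0.85 × 0.80 = 32%. The matching cumulative incidences, 13.5% and 18.5%, add to 32%.

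**The case against.** The line in Section 10.5 is generic. It lists no endpoints and no censoring rule, and it could be meant for all-cause mortality alone. Matching methods to endpoints is often left to a statistical analysis plan, which was not available. A reader might infer that Kaplan-Meier is fixed for every secondary endpoint, or that the reported risks are overstated. The protocol supports neither reading: six of the eight endpoints are defined as proportions, and a crude proportion is not inflated by competing death. It also nowhere describes pauses, bradycardia or AV block as time-to-event outcomes.

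A reader might also infer that the bias can only go upwards. That holds only if the remaining censoring is independent. Observation also ends when a new device is implanted (Section 7.1.5), and a patient can be discontinued for worsening primary disease (Section 7.6). Censoring of that kind may be informative and could shift a Kaplan-Meier estimate either way, including the one for all-cause mortality. Aalen-Johansen does not cure that, and once there is censoring it too can differ from the crude proportion.

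Finally, the study is exploratory, no decision threshold is attached to a secondary endpoint, and the effect is below the sampling error.

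These points limit the wording and the weight of the concern. What remains is that Kaplan-Meier is the only risk estimator named under the secondary analysis, and that a plan written from that line would inherit a method that fits one of the eight endpoints well.

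**Conclusion.** The point holds in conditional form: if the Kaplan-Meier line is applied to cardiovascular death or to a non-fatal endpoint with competing deaths censored, the resulting risk is at or above the cumulative incidence, given otherwise independent censoring. Under the assumed rates the excess is about 0.1 to 5.8 points at 3 years and under 1 point at 1 year. All of these sizes depend on assumed event and death rates and on constant hazards; the protocol supplies none of these. The primary endpoint is not touched, and no conclusion of the study turns on the difference. It is a minor improvement, worth making because it is cheap and removes an avoidable inconsistency between reported figures.

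**What to change.** In Section 10.5, item 3:

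- Keep Kaplan-Meier for all-cause mortality.
- Where a time-to-event risk is reported for cardiovascular mortality, use the Aalen-Johansen cumulative incidence with non-cardiovascular death as the competing event.
- For stroke, cardiovascular or heart failure hospitalisation, and device, ablation or antiarrhythmic therapy, use it with death as the competing event.
- If pauses, bradycardia or AV block are analysed as time-to-event, treat both death and device implantation that ends loop-recorder observation (Section 7.1.5) as competing events.
- Keep the Cox models and label them cause-specific.

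The cost is a few lines of text and a standard software routine, with no new data. The downside is that reported risks come out slightly lower.

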**10.6 Final Analysis**

- Conducted after all subjects complete the three-year follow-up.
- The study database will be locked, and results will be compiled into a final report.

**11. Items Related to Viewing of Original Materials**

In this study, “original materials” refers to medical records, various test data, records of prescriptions, etc.

Both the Principal Investigator and the administrator of each participating medical institution will agree to accept any monitoring and auditing related to this study, as well as investigations by the Certified Clinical Research Review Board and regulatory authorities. At such times, they guarantee that all relevant materials (including original materials) pertaining to this study will be made available for direct inspection.

For data documented in the case report form (CRF) which are not listed in the medical records, the following items will be treated as the original data within the CRF:

1. The purpose for the use of concomitant drugs (or therapies) and the purpose for conducting concomitant therapies
2. The severity, grade, outcome, date of outcome, and causal relationship with the investigational device for adverse events (or diseases, etc.), along with the reasons for determining the causality to the investigational device
3. The date of discontinuation, the reason for discontinuation, the adverse event or malfunction leading to discontinuation, and the subsequent course and results of follow-up after discontinuation
4. Comments by the Principal Investigator (or Sub-Investigator)

**12. Quality Control and Quality Assurance**

### 12.1 Monitoring

The Principal Investigator will develop a monitoring procedure manual for the purpose of quality control of this study and obtain review and approval from the Certified Clinical Research Review Board together with the study protocol. The Principal Investigator will also appoint a monitor responsible for carrying out the monitoring. The monitor will follow the monitoring procedure manual to verify, throughout the duration of the study, that this study is being conducted in compliance with the latest version of the study protocol and regulatory requirements (the Clinical Research Act, its enforcement regulations, etc.), and will report the findings to the Principal Investigator in accordance with the procedure manual. The monitor must not disclose any personal information of the study participants obtained through monitoring.

### 12.2 Auditing

Auditing of this study will be conducted by the Health Science R&D Center of Tokyo Medical and Dental University.

In order to ensure that all aspects of the study, as well as the creation, recording, and reporting of data, are conducted in compliance with the Clinical Research Act and its related regulations (including the enforcement regulations), the approved study protocol, and relevant procedural documents, the Principal Investigator will have an independent person perform the audit.

Specific methods and details of the audit will follow an auditing procedure manual established separately.

**13. Ethical Considerations**

### 13.1 Compliance with Laws and Regulations

All researchers involved in this study will conduct the trial in accordance with the “Declaration of Helsinki” (Japanese Medical Association translation)1) and the “Clinical Research Act” (Act No. 16 of 2017)2) and its enforcement regulations, as well as relevant notifications.

1. <http://dl.med.or.jp/dl-med/wma/helsinki2013j.pdf>
2. <http://www.mhlw.go.jp/stf/seisakunitsuite/bunya/0000163417.html>

### 13.2 Anticipated Benefits, Burdens, and Disadvantages

1. **Anticipated Benefits**
   Participation in this study will not result in any direct benefits to participants. However, the study findings could potentially contribute to the advancement of medical care in the future.
2. **Anticipated Disadvantages**
   The investigational medical device “Medtronic LINQ II” is a Class IV highly controlled medical device approved in Japan. Its use in this study population will be off-label; however, since it will be used in accordance with the instructions for use, given that it is a device for measuring electrocardiograms and is implanted subcutaneously, the burden on the study participants is considered limited. The likelihood of severe physical risk stemming from this study is deemed low.
   According to the instructions for use, device malfunctions such as early battery depletion, sensing failure, and data collection failure (frequency unknown) have been reported. There have also been reports of adverse events (frequency unknown) such as device extrusion, hematoma, bleeding, etc. Other unknown or known side effects or malfunctions may occur. If any side effects or malfunctions are observed, study personnel will administer appropriate care and provide the best possible treatment. The Principal Investigator will collect safety information and take appropriate actions, such as amending the study protocol if necessary.
3. **Anticipated Burdens**
   The number of clinic visits, tests, and the time required for examinations and tests in this study are roughly the same as those in standard medical care. There is no cost to participants for using the investigational device in this study (see “15. Payment of Money and Compensation” for details).
4. **Measures to Minimize Risks**
   This study targets outpatients as participants, and the likelihood of significant physical risk resulting from the study is considered low. Nevertheless, at each visit, the Principal Investigator (or Sub-Investigator) will be attentive to the participant’s condition and strive for early detection of any adverse events or malfunctions.

### 13.3 Handling of Genetic or Incidental Findings Related to Study Participants

This study does not involve any tests or analyses that would yield critical information about the participants’ health or genetic characteristics.

**14. Handling and Storage of Records (Including Data) and Samples**

### 14.1 Method of Data Collection

For this study, research data will be entered and managed in the electronic data capture (EDC) system “eACReSS.” The entered information will be stored on the eACReSS server at Tokyo Medical and Dental University.

Note: “eACReSS” is a dedicated clinical research data management system developed under the University Hospital Clinical Trial Alliance project. This alliance involves eight national universities in the Kanto-Koshinetsu area (the University of Tokyo, Chiba University, Tokyo Medical and Dental University, the University of Tsukuba, Gunma University, Niigata University, Shinshu University, and the University of Yamanashi).

1. **Storage location:** Inside the Tokyo Medical and Dental University “eACReSS” server
2. **Storage supervisor:** [name] (Health Science R&D Center, Tokyo Medical and Dental University)
3. **Storage period:** 10 years after the completion of the study
4. **Destruction method:** Data will be destroyed in a way that makes restoration impossible.
5. **Possibility of secondary use:** □ None ■ Yes (see “21.2 Secondary Use of Data”)

### 14.2 Retention of Records

1. The records that must be retained for this study include the following:
   (1) Date and location where the investigational medical product, etc. was used for each participant
   (2) Items identifying the study participants
   (3) Information pertaining to treatment and tests administered to the study participants
   (4) Information regarding participation in this study
   (5) Other items necessary for conducting this study
2. The Principal Investigator must keep, for 10 years from the day this study is completed, all records that must be retained for this study together with the following documents:
   (1) Study protocol, implementation plan, documents related to explanation and consent of participants, the final report, and any other documents created by the Principal Investigator under the Clinical Research Act and its enforcement regulations, or copies of such documents
   (2) Documents pertaining to review opinions from the Certified Clinical Research Review Board
   (3) Documents related to monitoring and auditing (if auditing is conducted)
   (4) Original materials, etc.
   (5) Contracts related to the implementation of this study (excluding those contracts concluded with marketing authorization holders of pharmaceutical products, etc., or their special related parties as stipulated in Article 32 of the Clinical Research Act)
   (6) Documents describing the overview of the investigational medical product, etc. used in this study, as well as documents related to the manufacturing, acquisition, and disposal of these products
   (7) Other documents necessary for conducting this study
3. If any corrections are made to the items (1)–(5) in the retained records for this study, the name of the person making the correction and the date the correction was made must be documented, and the corrected record must be retained together with that documentation.

### 14.3 Storage of Samples

In this study, there are no plans to collect, use, or store specimens (blood, tissues, cells, bodily fluids, excreta, or DNA extracted from any of these).

### 14.4 Storage and Disposal of Information

Any study-related documentation aside from what is managed in “eACReSS” will be stored in a lockable filing cabinet, inaccessible to anyone other than the researchers in the Department of Cardiology. These materials will be kept for 10 years after study completion (person responsible for storage: the Principal Investigator). Other materials will be handled and retained appropriately according to the procedures of each participating medical institution.

Moreover, the information and data collected in this study will be stripped of personal identifiers (such as name, initials, patient ID) and replaced with a new code so that individuals cannot be identified, all under the responsibility of the Principal Investigator. After the storage period is over, any electronic data will be destroyed in a way that makes restoration impossible, and any paper documents will be shredded, paying attention to personal information. If each participating medical institution has separate procedures for disposal, those procedures will be followed.

**15. Payment of Money and Compensation**

### 15.1 Payment of Money (Participant’s Expenses)

In this study, the investigational device provided by Medtronic Japan Co., Ltd. will be used. Therefore, participants will not incur any costs for the investigational device (including ILR implantation and remote monitoring). The costs of tests and examinations conducted in this study are the same as those in standard medical care.

### 15.2 Compensation

If a participant in this study sustains health damage as a result of the study, the Principal Investigator, Sub-Investigators, and the participating medical institution will promptly ensure that the participant receives the appropriate diagnosis, treatment, and any other necessary measures. The Principal Investigator carries clinical research insurance with the coverage listed below, which will be applied in accordance with the insurance payment conditions to compensate for any losses suffered by the participant due to health damage resulting from the study (excluding cases where the participant is at fault):

- Compensation for death or permanent disability of the participant
- Medical expenses and medical allowances necessary for treating health damage of the participant

Additionally, the Principal Investigator and Sub-Investigators must be enrolled in medical malpractice liability insurance to cover potential health damages to participants arising from the normal scope of medical practice during this study.

**16. Disclosure of Information**

Before conducting this study, the required information set forth by the World Health Organization (WHO) to ensure the transparency of clinical research, as well as items that help the public make informed decisions about participating in clinical research, will be registered in jRCT and disclosed. The study will commence after disclosure in jRCT, and the information will be updated as needed depending on any changes to the implementation plan or progress of the study. Additionally, if a main outcome report or final study report is created, an outline of such a report will be made public.

